## 7.6.2 Secondary efficacy evaluation

### 7.6.2.1 Secondary protective efficacy evaluation

**(1) Protective efficacy of the study vaccine against first occurrence of all infections, obvious symptomatic infection of SARS-CoV-2, respectively, starting 7 days post vaccination ( $\geq 8$  days) versus placebo**

Statistical analysis is performed on the protective efficacy of the study vaccine against first occurrence of all infections and obvious symptomatic infection of SARS-CoV-2, respectively, 7 days post vaccination ( $\geq 8$  days) versus placebo based on PPE using the same analytical methods as used for the primary efficacy evaluation.

Sensitivity analysis is performed on the protective efficacy of the study vaccine against first occurrence of all infections and obvious symptomatic infection of SARS-CoV-2, respectively, 7 days post vaccination ( $\geq 8$  days) versus placebo based on PPE using the same sensitivity analysis method as used for the primary efficacy evaluation.

**(2) Protective efficacy of the study vaccine against first occurrence of all infections of SARS-CoV-2 (including asymptomatic infection) starting 7 days post vaccination ( $\geq 8$  days) versus placebo**

Statistical analysis is performed on the protective efficacy of the study vaccine against all infections of SARS-CoV-2 (including asymptomatic infection) occurring for the first time after 7 days post vaccination ( $\geq 8$  days) versus placebo based on PPE using the same analytical methods as used for the primary efficacy evaluation.

Sensitivity analysis is performed on the protective efficacy of the study vaccine against all infections of SARS-CoV-2 (including asymptomatic infection) occurring after 7 days post vaccination ( $\geq 8$  days) versus placebo based on PPE using the same sensitivity analysis method as used for the primary efficacy evaluation.

**(3) Protective efficacy of the study vaccine against asymptomatic SARS-CoV-2 infection occurring for the first time after 7 days post vaccination ( $\geq 8$  days) versus placebo**

Statistical analysis is performed on the protective efficacy of the study vaccine against asymptomatic SARS-CoV-2 infection occurring for the first time after 7 days post vaccination ( $\geq 8$  days) versus placebo based on PPE using the same analytical methods as used for the primary efficacy evaluation.

Sensitivity analysis is performed on the protective efficacy of the study vaccine against asymptomatic SARS-CoV-2 infection occurring for the first time after 7 days post vaccination ( $\geq 8$  days) versus placebo based on PPE using the same sensitivity analysis method as used for the primary efficacy evaluation.

**(4) Protective efficacy of the study vaccine against moderate and above COVID-19 with SARS-CoV-2 infection occurring for the first time after 7 days post vaccination ( $\geq 8$  days) versus placebo**

Statistical analysis is performed on the protective efficacy of the study vaccine against moderate and above COVID-19 occurring for the first time after 7 days post vaccination ( $\geq 8$  days) versus placebo based on PPE using the same analytical methods as used for the primary efficacy evaluation.

**(5) Protective efficacy of the study vaccine against severe and above COVID-19 occurring for the first time after 7 days post vaccination ( $\geq 8$  days) versus placebo**

Statistical analysis is performed on the protective efficacy of the study vaccine against severe and above COVID-19 occurring for the first time after 7 days post vaccination ( $\geq 8$  days) versus placebo based on PPE using the same analytical methods as used for the primary efficacy evaluation.

**(6) Protective efficacy of the study vaccine against COVID-19-induced death occurring for the first time after 7 days post vaccination ( $\geq 8$  days) versus placebo**

Statistical analysis is performed on the protective efficacy of the study vaccine against COVID-19-induced death occurring for the first time after 7 days post vaccination ( $\geq 8$  days) versus placebo based on PPE using the same analytical methods as used for the primary efficacy evaluation.

**(7) Protective efficacy of the study vaccine against symptomatic infection of SARS-CoV-2 after 14 days post vaccination ( $\geq 15$  days) versus placebo**

Statistical analysis is performed on the protective efficacy of the study vaccine against symptomatic infection of SARS-CoV-2 after 14 days post vaccination ( $\geq 15$  days) versus placebo based on PPE-14 using the same analytical methods as used for the primary efficacy evaluation.

Sensitivity analysis is performed on the protective efficacy of the study vaccine against symptomatic infection of SARS-CoV-2 after 14 days post vaccination ( $\geq 15$  days) versus placebo based on PPE-14 using the same sensitivity analysis method as used for the primary efficacy evaluation.

**(8) Protective efficacy of the study vaccine against obvious symptomatic infection of SARS-CoV-2 after 14 days post vaccination ( $\geq 15$  days) versus placebo**

Statistical analysis is performed on the protective efficacy of the study vaccine against obvious symptomatic infection of SARS-CoV-2 for the first time after 14 days post vaccination ( $\geq 15$  days) versus placebo based on PPE-14 using the same analytical methods as used for the primary efficacy evaluation.

Sensitivity analysis is performed on the protective efficacy of the study vaccine against obvious symptomatic infection of SARS-CoV-2 for the first time after 14 days post vaccination ( $\geq 15$  days) versus placebo based on PPE-14 using the same sensitivity analysis method as used for the primary efficacy evaluation.

**(9) Protective efficacy of the study vaccine against all infections of SARS-CoV-2 (including asymptomatic infection) occurring for the first time after 14 days post vaccination ( $\geq 15$  days) versus placebo**

Statistical analysis is performed on the protective efficacy of the study vaccine against all infections of SARS-CoV-2 (including asymptomatic infection) occurring for the first time after 14 days post vaccination ( $\geq 15$  days) versus placebo based on PPE-14 using the same analytical methods as used for the primary efficacy evaluation.

Sensitivity analysis is performed on the protective efficacy of the study vaccine against all infections of SARS-CoV-2 (including asymptomatic infection) occurring after 14 days post vaccination ( $\geq 15$  days) versus placebo based on PPE-14 using the same sensitivity analysis method as used for the primary efficacy evaluation.

**(10) Protective efficacy of the study vaccine against asymptomatic SARS-CoV-2 infection occurring for the first time after 14 days post vaccination ( $\geq 15$  days) versus placebo**

Statistical analysis is performed on the protective efficacy of the study vaccine against asymptomatic SARS-CoV-2 infection occurring for the first time after 14 days post vaccination ( $\geq 15$

days) versus placebo based on PPE-14 using the same analytical methods as used for the primary efficacy evaluation.

Sensitivity analysis is performed on the protective efficacy of the study vaccine against asymptomatic SARS-CoV-2 infection occurring for the first time after 14 days post vaccination ( $\geq 15$  days) versus placebo based on PPE-14 using the same sensitivity analysis method as used for the primary efficacy evaluation.

**(11) Protective efficacy of the study vaccine against symptomatic infection of SARS-CoV-2 caused by SARS-CoV-2 variants and subvariants occurring for the first time after 14 days post vaccination ( $\geq 15$  days) versus placebo**

Statistical analysis is performed on the protective efficacy of the study vaccine against symptomatic infection of SARS-CoV-2 caused by SARS-CoV-2 variants and subvariants occurring for the first time after 14 days post vaccination ( $\geq 15$  days) versus placebo based on PPE-14 using the same analytical methods as used for the primary efficacy evaluation.

**(12) Protective efficacy of the study vaccine against obvious symptomatic infection of SARS-CoV-2 caused by SARS-CoV-2 variants and subvariants occurring for the first time after 14 days post vaccination ( $\geq 15$  days) versus placebo**

Statistical analysis is performed on the protective efficacy of the study vaccine against obvious symptomatic infection of SARS-CoV-2 caused by SARS-CoV-2 variants and subvariants occurring for the first time after 14 days post vaccination ( $\geq 15$  days) versus placebo based on PPE-14 using the same analytical methods as used for the primary efficacy evaluation.

**(13) Protective efficacy of the study vaccine against moderate and above COVID-19 caused by SARS-CoV-2 variants and subvariants occurring for the first time after 14 days post vaccination ( $\geq 15$  days) versus placebo**

Statistical analysis is performed on the protective efficacy of the study vaccine against moderate and above COVID-19 caused by SARS-CoV-2 variants and subvariants occurring for the first time after 14 days post vaccination ( $\geq 15$  days) versus placebo based on PPE-14 using the same analytical methods as used for the primary efficacy evaluation.

**(14) Protective efficacy of the study vaccine against severe and above COVID-19 caused by SARS-CoV-2 variants and subvariants occurring for the first time after 14 days post vaccination ( $\geq 15$  days) versus placebo**

Statistical analysis is performed on the protective efficacy of the study vaccine against severe and above COVID-19 caused by SARS-CoV-2 variants and subvariants occurring for the first time

after 14 days post vaccination ( $\geq 15$  days) versus placebo based on PPE-14 using the same analytical methods as used for the primary efficacy evaluation.

**(15) Protective efficacy of the study vaccine against COVID-19-induced death caused by SARS-CoV-2 variants and subvariants occurring for the first time after 14 days post vaccination ( $\geq 15$  days) versus placebo**

Statistical analysis is performed on the protective efficacy of the study vaccine against COVID-19-induced death caused by SARS-CoV-2 variants and subvariants occurring for the first time after 14 days post vaccination ( $\geq 15$  days) versus placebo based on PPE-14 using the same analytical methods as used for the primary efficacy evaluation.

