### 4.3 Sample size

After the adjustment of Beijing epidemic prevention and control policy, the protective efficacy of SCTV01E is between 70% and 77% in the real-world study. Therefore, assuming a protective efficacy (VE) of 70% (Hazard Ratio = 0.3) for the PPE population (as defined in the Analysis Set section) 7 days post-vaccination, in the condition of 59 cases, there is approximately 90% power to reject the null hypothesis  $H_0$  at a one-sided Type I error level of 0.025. The following assumption will be considered for sample size estimation and approximately 10000 participants (adjusted for actual infection rates) will be included. The final number of participants enrolled depends on the actual infection rate and the cumulative number of COVID-19 events. Of these participants, 5%–10% will be included in the immunogenicity subgroup.

- In the control group, the symptomatic infection of SARS-CoV-2 within 1 month is about 1.5%.
- The dropout rate during the study is about 10%.
- Approximately 15% of participants could not be included in the assessment of the number of events after 7 days because they are PCR positive at baseline or have an infection within 0–7 days after vaccination.

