#### **7.6 Efficacy evaluation**

##### **7.6.1 Primary efficacy evaluation**

✧ **Protective efficacy of the study vaccine against symptomatic infection of SARS-CoV-2 after 7 days post vaccination ( $\geq 8$  days) versus placebo**

The Cox proportional hazards model is used to statistically analyze the protective efficacy of the study vaccine against symptomatic infection of SARS-CoV-2 after 7 days post-vaccination, with the person-years at risk as the dependent variable and with the age (18–59 years,  $\geq 60$  years), the vaccine type of the last previous dose (inactivated, non-inactivated), and the group as fixed effects. The protection rate of the vaccine and its 95% confidence interval are calculated according to the model. Events that coincide in time are handled based on the Efron method. If the model reaches convergence, the stratification factor of the vaccine type of the last previous dose will be removed from the model first; if the model still converges, the age stratification factor will be further removed.

Person-years at risk of the primary endpoints = (End/censored time of valid case surveillance period - Vaccination time - 7) / 365.25; where, the end/censored time of valid case surveillance period is calculated according to the following rules:

- For those who have symptoms and are diagnosed with COVID-19 before the data cut-off date, the end time is the start date of the first symptom (first onset date) of the target event or the date of the positive result for antigen or nucleic acid tests corresponding to the event, whichever comes earlier;
- For those with positive results of rapid antigen and/or laboratory RT-PCR tests post vaccination before the data cut-off date, but not diagnosed with the target event, the censored time is the earlier of the sampling dates corresponding to the positive results for antigen and RT-PCR tests;
- For those with negative results of rapid antigen and/or laboratory RT-PCR test post vaccination before the data cut-off date, but not diagnosed with the target event, the censored time is the last follow-up date of the case surveillance;
- For those vaccinated with other COVID-19 vaccines before the data cut-off date, the censored time is the date of first vaccination with other COVID-19 vaccines; those diagnosed with target events after vaccination with other COVID-19 vaccines are not included in the case count.

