### **7.9 Subgroup analysis**

If data permit, the following subgroups will be analyzed separately for protective efficacy and

immunogenicity:

- Age (18–59 years,  $\geq 60$  years)
- Sex (male, female)
- Time since last previous vaccination (6–12 months, 13–24 months)
- Vaccine type of the last previous dose (inactivated, non-inactivated)

In particular, if the model does not converge due to too few observed events during subgroup analysis, the factor of groups is only retained in the subgroup analysis model.

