### **7.11 Interim analysis**

There will be no planned interim analysis plan for this study. The study will conduct a final analysis of the primary endpoint at a one-sided significance level of 0.025 when at least 59 target events for the primary endpoint have accumulated. This analysis will be performed by an independent third party and the sponsor will establish an unblinded submission team to complete the submission. Investigators, participants, and team members directly involved in the project will remain blinded for long-term protective efficacy and safety follow-up.

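### The SAP names no confidence interval that survives an empty vaccine arm for moderate, severe and fatal COVID-19, and does not extend its own exact Poisson analysis to these endpoints

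*Combined protocol and SAP*

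**What the plan says.** - **Method for the severe endpoints.** SAP 7.6.2.1 items (4)-(6) cover moderate-and-above disease, severe-and-above disease and COVID-19 death from 7 days after vaccination, analysed "based on PPE using the same analytical methods as used for the primary efficacy evaluation". Items (13)-(15) cover the same outcomes caused by variants from 14 days, "based on PPE-14 using the same analytical methods as used for the primary efficacy evaluation".
- **The primary method.** SAP 7.6.1 uses a Cox model with Efron ties and terms for age, last vaccine type and group. On the interval it says only: "The protection rate of the vaccine and its 95% confidence interval are calculated according to the model". Wald, profile likelihood or another type is not specified.
- **Fallbacks.** SAP 7.6.1 drops last vaccine type and then age. As written this is triggered when the model does converge, presumably a slip for non-convergence. For subgroups, SAP 7.9 says that "if the model does not converge due to too few observed events during subgroup analysis, the factor of groups is only retained".
- **The exact method in the plan.** Sensitivity analysis 1 in SAP 7.6.1 is an exact Poisson regression with person-years as offset. SAP 7.6.2.1 carries the sensitivity analyses to items (1)-(3) and (7)-(10), but not to (4)-(6) or (11)-(15).
- **Timing.** SAP 7.11 sets the final analysis "when at least 59 target events for the primary endpoint have accumulated".
- **Status.** SAP 7.10 leaves these endpoints outside the ten-step hierarchy, so their P values are nominal.

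**The concern.** The rarest outcomes are given a large-sample estimator, while the plan's one small-sample method is reserved for commoner outcomes. If the vaccine arm has no case, the Cox partial likelihood keeps rising as the hazard ratio falls towards 0, so the group coefficient has no finite maximum. Removing covariates does not help, because group is the term that fails. SAP 7.9 shows that too few events were foreseen, but its remedy keeps exactly that term.

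Protection against moderate, severe and fatal disease is a stated secondary objective. With no rule for an empty arm, the interval would have to be chosen after the case split is known, and that choice can decide whether the interval excludes 0%.

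**Working it through.** **Inputs.** At least 59 primary cases (SAP 7.11); 1:1 allocation (SAP 4.2); design effect "assuming a protective efficacy (VE) of 70% (Hazard Ratio = 0.3) for the PPE population", null VE 30%, one-sided 0.025 and 90% power (SAP 4.3 and 7.5). The share f of placebo symptomatic cases that reach a given severity is an **assumption**, shown as a range.

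**1. The plan's own figure.** SAP 4.3 states that with 59 cases "there is approximately 90% power to reject the null hypothesis". Schoenfeld: (1.960 + 1.282)² / [0.25 × (ln(0.3/0.7))²] = 10.51 / 0.1795 = 58.5, so 59 events; power at 59 is 90.2%. The figure reproduces.

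**2. Case split.** At VE 70%: placebo 59/1.3 = 45.4, vaccine 59 × 0.3/1.3 = 13.6.

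**3. Chance of an empty vaccine arm.** Poisson means: placebo 45.4 × f; vaccine 45.4 × f × (1 - VE), where VE is that against the outcome in question. P(zero vaccine cases) = exp(-vaccine mean). P(no case in either arm) = exp(-total mean).

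| f | VE 70%: expected total | VE 70%: P(zero vaccine) | of which no case in either arm | VE 90%: P(zero vaccine) |
|---|---|---|---|---|
| 1% | 0.59 | 87% | 55% | 96% |
| 2% | 1.18 | 76% | 31% | 91% |
| 5% | 2.95 | 51% | 5% | 80% |
| 10% | 5.90 | 26% | 0.3% | 64% |

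The difference of the third and fourth columns is the chance at VE 70% that placebo has cases and vaccine has none, where the interval type matters: about 32%, 45%, 45% and 25%.

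For death there is a check in the reported data. Table S6 lists one death of any cause on placebo and none on SCTV01E, so a COVID-19 death comparison in those data has an empty vaccine arm.

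**4. What the Cox fit returns.** Efron fits to simulated data (1,300 per arm, no vaccine case) gave, for 1, 3 and 5 placebo cases, log HR of -25.2, -28.9 and -25.2 with standard errors of about 303,000, 1,084,000 and 135,000. With 10 placebo cases the fit failed. A Wald interval from these is 0 to infinity for the hazard ratio.

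**5. Two intervals that do exist for 0 versus k cases** (equal person-time):
- Profile likelihood: the log likelihood is about -k × ln(1 + HR), so the upper HR limit is exp(1.92/k) - 1.
- Exact conditional: u = 1 - 0.025^(1/k), and the upper HR limit is u/(1 - u).

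| k placebo cases | Lower VE limit, profile | Lower VE limit, exact |
|---|---|---|
| 1 | -483% | -3800% |
| 3 | +10% | -142% |
| 5 | +53% | -9% |
| 6 | +62% | +15% |
| 8 | +73% | +41% |
| 10 | +79% | +55% |

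Profile limits taken directly from the simulated fits were -493%, +11%, +53% and +79% for k = 1, 3, 5 and 10.

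The gap has a simple source. At the profile limit the chance of zero vaccine cases among k is (1 + HR)^(-k) = exp(-1.92) = 0.147; at the exact limit it is 0.025. With an empty arm, the profile limit is therefore not a 2.5% tail bound.

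**6. What the exact interval can show.** The lower limit exceeds 0% only from 6 versus 0. The chance of zero vaccine and at least 6 placebo cases at VE 70% is about 0.001% (f = 1%), 0.03% (2%), 1.4% (5%) and 8% (10%).

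**The case against.** Several stronger readings are tempting, and the documents do not support them.

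- *The Cox model cannot give an interval.* This is true of the Wald interval only. The SAP does not name the type, and a profile-likelihood interval from the same model has a finite lower VE limit once placebo has a case. What stands is that the type is left open and the conclusion depends on it.
- *These endpoints will have almost no events.* The documents give no severity share. The reading is reasonable for f up to about 2%, weaker at 5%, and wrong at 10%, where about 6 cases are expected.
- *The secondary objectives return no usable result.* The count of 59 is a minimum, and SAP 7.11 continues blinded efficacy follow-up, so later cuts may hold more cases. The sparsity at the first cut comes from the number of cases and would remain under any interval.
- *All of items (11)-(15) are affected.* Items (11) and (12) concern symptomatic and obvious symptomatic infection caused by variants, and nothing in the documents shows these to be sparse.

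It is also fair to say that the endpoints are nominal, that subgroup analyses are already conditional on the data permitting them, and that the protocol synopsis refers sensitivity-analysis details to protocol section 11.4.4, which is not among the documents reviewed. The gap is shown for the SAP and synopsis only. These points limit the consequence, but a nominal estimate still needs a defined interval.

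**Conclusion.** The point holds as a should-fix gap in method. For items (4)-(6) and (13)-(15) the SAP prescribes a model whose usual interval fails when the vaccine arm is empty, offers fallbacks that cannot cure this, and does not extend its own exact analysis to them. At VE 70% an empty vaccine arm has probability 87% to 51% for f from 1% to 5%, and 26% at 10%. These figures rest on the assumed f, on exactly 59 cases and on Poisson counts, and they include outcomes with no case at all, where no method estimates VE.

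The practical stake is an unspecified choice that can move the lower limit from -9% to +53% at 0 versus 5. Interpretation of nominal secondary endpoints is affected; the primary test and the ten-step hierarchy are not.

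**What to change.** In SAP 7.6.2.1, for items (4)-(6) and (13)-(15), and for any subgroup in 7.9 with an empty arm:

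1. Extend Sensitivity analysis 1 to these analyses (exact Poisson, or the exact conditional interval for the case split given person-years at risk, with VE as 1 minus the rate ratio), and make it the reported interval whenever either arm has zero cases.
2. If neither arm has a case, report counts and rates only.
3. Name the type of the Cox interval in 7.6.1, and reword the convergence trigger there so that it applies when the model fails to converge.

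If protocol section 11.4.4 already holds such a rule, carry it into the SAP.

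The cost is a few sentences, since the exact Poisson analysis is already planned for other endpoints. The exact interval is slightly conservative and may be unadjusted for the stratification factors. It makes the result reportable without adding information: at least 6 versus 0 cases are still needed to exclude a VE of 0%.
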